# Evaluation of the efficacy and safety of conventional and biportal endoscopic decompressive laminectomy in patients with lumbar spinal stenosis (ENDO-B trial): a protocol for a prospective, randomized, assessor-blind, multicenter trial

**DOI:** 10.1186/s12891-021-04959-2

**Published:** 2021-12-20

**Keywords:** Lumbar spinal stenosis, Biportal endoscopic spine surgery, Decompressive laminectomy

## Abstract

**Background:**

Recent studies on biportal endoscopic spine surgery in patients with lumbar spinal stenosis have reported good clinical results. However, these studies have been limited by the small sample sizes and use of a retrospective study design. Therefore, we aim to compare the efficacy and safety of biportal endoscopic decompressive laminectomy with those of conventional decompressive laminectomy in a multicenter, prospective, randomized controlled trial.

**Methods:**

This study will include 120 patients (60 per group, aged 20–80 years) with 1- or 2-level lumbar spinal stenosis, who will be recruited from six hospitals. The study will be conducted from July 2021 to December 2024. The primary outcome (Oswestry Disability Index at 12 months after surgery) will be evaluated through a modified intention-to-treat method. The secondary outcomes will include the following: visual analog scale score for low back and lower extremity radiating pain, EuroQol 5-dimensions score, surgery satisfaction, walking time, postoperative return to daily life period, postoperative surgical scars, and some surgery-related variables. Radiographic outcomes will be analyzed using magnetic resonance imaging or computed tomography. All outcomes will be evaluated before the surgery and at 2 weeks, 3 months, 6 months, and 12 months postoperatively. This protocol adheres to the Standard Protocol Items: Recommendations for Interventional Trials (SPIRIT) guidelines for reporting of clinical trial protocols.

**Discussion:**

It is hypothesized that the efficacy and safety of biportal endoscopic and conventional decompressive laminectomy will be comparable in patients with lumbar spinal stenosis. The results of this trial will provide a high level of evidence for the efficacy and safety of the biportal endoscopic technique in patients with lumbar spinal stenosis and facilitate the development of clinical practice guidelines. Furthermore, the results of this study may indicate the feasibility of the biportal endoscopic technique for other types of spinal surgery.

**Trial registration:**

The ENDO-B trial is registered at Clinical Research Information Service (CRIS, cris.nih.go.kr) (KCT0006057; April 52,021).

## Background

Lumbar spinal stenosis (LSS) is a disease that causes several symptoms, such as low back pain and intermittent claudication, due to the narrowing of the central spinal canal, nerve root canal, or intervertebral space [1]. With an aging demographic, surgical treatment for LSS has become increasingly common. Among the various surgical approaches for this condition, decompressive laminectomy is the most frequently used method [2]. However, this conventional method has been associated with complications such as intraoperative bleeding, postoperative pain, instability, and damage of the paraspinal muscles [3]. An emerging alternative method is minimally invasive surgery, which preserves the existing anatomical structures. The most frequently used minimally invasive surgery is unilateral laminectomy bilateral decompression (ULBD) [4, 5]. Compared with conventional laminectomy, ULBD showed comparable clinical outcomes, and it was superior in terms of postoperative recovery time, time to mobilization, and opioid use [2, 6].

In 1973, Parvis Kambin introduced the concept of a transforaminal approach, which involves the percutaneous placement of Craig’s cannula. In 1991, he performed the first endoscopic spine surgery using a cannula for interlaminar and transforaminal endoscopy [7]. Endoscope-assisted spinal surgery has several advantages, such as less approach-related trauma, preservation of the epidural blood supply, and reduced epidural scarring and fibrosis compared to those performed with conventional methods [8]. The biportal endoscopic spine surgery, first introduced by Soliman in 2013, is a technique that permits the free movement of instruments through the two portals [9]. It has a good field of view, as the camera can be placed at various angles; this facilitates safe and sufficient decompression. Furthermore, the equipment used for the knee and shoulder arthroscope can be used for the spine without the need for additional changes in settings. Moreover, it allows the use of the same instruments as in conventional spine surgery. Since the biportal endoscopic technique only requires small incisions of less than 1 cm, damage to the surrounding normal tissues is minimized; this results in fewer complications, such as pain and adhesion, after surgery.

Previous studies evaluating the use of the biportal endoscopic technique in LSS surgery have reported good clinical results; however, the strength of evidence has been limited by the use of a retrospective study design and small sample sizes [10, 11]. There is currently a lack of level 1 studies to establish the efficacy and stability of the biportal endoscopic technique in comparison with conventional methods. Therefore, we aim to compare the efficacy and safety of biportal endoscopic decompressive laminectomy with those of conventional decompressive laminectomy in a multicenter, prospective randomized controlled trial (RCT). Our hypothesis is that the efficacy and safety of these two methods are similar in patients with LSS.

## Methods/design

### Study design and inclusion criteria

The design and protocol of this multicenter, assessor-blind, prospective RCT were approved by the institutional review board of the participating hospitals from Korea. From July 2021 to December 2024, a total of 120 adults (aged 20–80 years) with radiating pain in the lower extremities or neurogenic claudication will be recruited from six hospitals. Patients will be included if they 1) have decided to undergo 1- or 2-level decompressive laminectomy for lumbar central canal stenosis, 2) are able to provide informed consent, and 3) are willing to participate and comply with our proposed follow-up protocol. The exclusion criteria were as follows: 1) spondylolisthesis (Meyer grade ≥ II), 2) a history of lumbar spinal surgery at the same level, 3) degenerative lumbar scoliosis (Cobb angle > 20°), 4) stenosis not caused by degeneration or intervertebral disc herniation, 5) other spinal diseases (e.g., ankylosing spondylitis, spine tumor, fracture, or neurologic disorders), 6) psychological disorders (e.g., dementia, intellectual disability, or drug abuse), 7) refusal to participate in the study, and 8) other disorders that the surgeon considers inappropriate for inclusion. This protocol adheres to the Standard Protocol Items: Recommendations for Interventional Trials (SPIRIT) guidelines for reporting of clinical trial protocols [12].

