### Randomization

The included patients will be randomly assigned (permuted block method) in a 1:1 ratio to either the biportal endoscopic group (case group) or conventional group (control group), following a computer-generated randomization list (Fig. 1). The randomization lists will be incorporated into a web-based electronic case report form (eCRF) platform (iCReaT; internet-based clinical research and trial, icreat.nih.go.kr) accessible to authorized researchers. To minimize bias, randomization will be performed by the research coordinator who is not involved in the treatment of the patients. Sixteen surgeons from six institutions will be informed of each patient’s group allocation via the randomization code immediately before surgery. Patients will be aware of their group allocation because of the incision site after surgery. This RCT will be single-blind (assessor-blind).

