#### Secondary outcomes

##### Clinical outcomes

Visual analog scale (VAS) score for low back pain and radiating pain of the lower extremities: scores range from 0 to 10; a higher score indicates more severe painPatient’s quality of life, as assessed by the EuroQol 5-dimensions questionnaire (EQ-5D): EQ-5D contains five questions with five responses for each question, and the total score is converted into the final EQ-5D value, ranging from 0.000 to 1.000; higher score indicates a better quality of life [15].Surgery satisfactionWalking timePostoperative return to daily life periodSurgical scars, as evaluated using the Patient and Observer Scar Assessment Scale 2.0, which contains six parameters with 10-point scoring system; 6 represents normal skin and 60 represents the worst scar imaginableSurgery-related variables, such as postoperative drainage (mL), operation time (minutes), admission duration (hours), and postoperative creatine kinase (International Unit/L)

Patient-reported outcomes will be collected from the participants at baseline and at 2 weeks, 3 months, 6 months, and 12 months after surgery.

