#### Sample size and statistical analysis

This trial will recruit 120 participants (60 participants per group) to confirm the primary outcome equivalence between biportal endoscopic and conventional decompressive laminectomy. Previous studies have indicated a minimal clinically important ODI difference of 12.8 [17], as well as a standard deviation of 18.8, at 1 year after endoscopic decompressive laminectomy [18]. A required sample size of 60 patients per group was determined based on these values and the following parameters: alpha of .05, power of .90, two-sided confidence interval of 95%, and a 20% loss to follow-up.

All statistical analyses will be performed using SPSS 26.0 (version 26.0, Chicago, IL, USA). A *P* value < .05 will be considered significant. A modified intention-to-treat (mITT) analysis will be used. The mITT strategy indicates that participants are analyzed on whether they underwent a randomly assigned surgery (to avoid the effects of crossover and dropout, which may disrupt the random assignment to the treatment groups). Participants who do not complete the follow-up schedule will be excluded from the analysis, and there will be no additional enrollment.

In each group, changes in secondary outcomes from baseline to follow-up will be analyzed with repeated measures analysis of variance. Differences in other clinical and radiologic outcomes, as well as adverse events, between the two groups will be analyzed using Student’s t-test (for continuous variables) and chi-square test (for categorical variables).

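### One- and two-level patients are enrolled together, but operation time, drainage, creatine kinase and admission duration are compared by an unadjusted t-test: a loss of precision, not of validity

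*Protocol article*

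**What the plan says.** - **Eligibility** (Study design and inclusion criteria): patients are included if they "have decided to undergo 1- or 2-level decompressive laminectomy for lumbar central canal stenosis". The Recruitment section repeats the one- or two-level rule for scheduled patients. The planned number of levels is therefore part of screening, and Table 1 places screening before randomisation.
- **Outcomes** (Secondary outcomes, Clinical outcomes): the surgery-related variables are "postoperative drainage (mL), operation time (minutes), admission duration (hours), and postoperative creatine kinase".
- **Analysis** (Sample size and statistical analysis): changes from baseline within each group go to a repeated-measures analysis of variance. Differences in other clinical outcomes "between the two groups will be analyzed using Student’s t-test (for continuous variables"), with a chi-square test for categorical ones. Operation time, drainage and admission duration have no baseline value, and creatine kinase is listed only as a postoperative value. The t-test is thus the only between-group method the article offers for them.
- **Allocation** (Randomization): patients are "randomly assigned (permuted block method) in a 1:1 ratio". No stratification factor is named, and allocation is not said to be unstratified.

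The article does not use number of levels in any adjustment or subgroup.

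**The concern.** The eligibility rule builds a known two-class mix into the trial. Both technique descriptions involve detaching paraspinal muscle and removing lamina and ligamentum flavum at the stenotic region. A second level plausibly adds operating time, drainage, creatine kinase release and perhaps stay. That is surgical reasoning; the article gives no figures for it.

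If number of levels does move these outcomes, an unadjusted comparison has two costs:

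1. The spread between one- and two-level patients is counted as noise, so the confidence interval for the technique difference is wider than it need be.
2. If one arm happens to receive more two-level patients, the observed difference shifts and the prespecified test has no means of correcting it. Adding an adjustment after the imbalance has been seen would be post hoc.

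The primary hypothesis is similarity on the Oswestry Disability Index (ODI), so readers will look to secondary outcomes for any practical difference between the techniques.

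**Working it through.** **The plan's own figure.** The article states a sample size only for the ODI. Inputs: difference 12.8, SD 18.8, alpha 0.05, power 0.90, 20% loss.

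- Two-sample normal formula: 2 × (18.8 × (1.960 + 1.282) / 12.8)² = 45.3, so 46 per arm; 46 / 0.8 = 57.5, so 58.
- Two one-sided equivalence tests at one-sided 0.05, t-based, true difference zero: 48 per arm; 48 / 0.8 = 60.

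The stated 60 per group is therefore reproduced to within two patients, and nothing below changes it. No figure is stated for the four outcomes at issue.

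**Assumed inputs.** The article gives neither of these:

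- p, the share of two-level patients: 20% to 50%.
- d, the two-level minus one-level mean difference in within-level SDs: 0.5 to 2.

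**Variance factor.** Ignoring a binary factor raises the outcome variance from 1 to F = 1 + p(1 − p)d².

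- Smallest: p = 0.2, d = 0.5: 1 + 0.16 × 0.25 = 1.04.
- Largest: p = 0.5, d = 2: 1 + 0.25 × 4 = 2.00.

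The confidence interval widens by √F, from 1.02 to 1.41 times.

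**Power.** Take an effect that has 80% power at two-sided 0.05 when levels are adjusted for. Its standardised size is 1.960 + 0.842 = 2.802. Ignoring levels, power = Φ(2.802/√F − 1.960).

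| d | F at p = 0.2 / 0.3 / 0.5 | Power at p = 0.2 / 0.3 / 0.5 |
|---|---|---|
| 0.5 | 1.04 / 1.05 / 1.06 | 78% / 78% / 78% |
| 1.0 | 1.16 / 1.21 / 1.25 | 74% / 72% / 71% |
| 1.5 | 1.36 / 1.47 / 1.56 | 67% / 64% / 61% |
| 2.0 | 1.64 / 1.84 / 2.00 | 59% / 54% / 51% |

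**Type I error.** Simulating random 1:1 splits of 120 patients (20,000 runs each; p = 0.3 and 0.5, d = 1 and 2) gave rejection rates of 4.8% to 5.1% for the unadjusted t-test. The test is valid.

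**Chance imbalance, only if allocation does not balance levels.** With 60 per arm and p from 0.2 to 0.5, the arms differ in two-level share by at least 10 percentage points in 25% to 36% of allocations (hypergeometric), and by at least 15 points in 4% to 10%. Treating the arms as independent binomials gives 21% to 32% and 5% to 12%. A 10-point imbalance shifts the observed difference by 0.10 × d, that is 0.05 to 0.20 within-level SDs.

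**If allocation does balance levels.** The imbalance disappears, but the t-test's standard error still carries the between-level spread. Power is then about Φ(2.802 − 1.960√F): 79% at F = 1.04 and 51% at F = 2.00. The test becomes conservative. The case for adjustment therefore does not depend on how the lists were built.

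**The case against.** The strongest reply is that nothing is broken. Randomisation makes the unadjusted difference unbiased, chance imbalance is ordinary sampling variation that the standard error already covers, and these are secondary outcomes with no power claim. All of that stands. It limits the point to efficiency and to interpretation of the particular allocation obtained.

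The second reply is that the size rests wholly on assumed inputs. This also stands: at a difference of 0.5 SD the loss is about two points of power, which is negligible. The range must be shown from that end.

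Several stronger readings are tempting, and the document does not support them:

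- **That randomisation ignores number of levels.** The Randomization section names no stratification factor, but it is part of a condensed article and such detail is commonly left to the full protocol. Silence does not establish it.
- **That these four outcomes are where the article expects the techniques to differ.** The Discussion cites less early pain, shorter stay, earlier ambulation, less opioid need and less segmental instability. Of the four, only hospital stay is among them. The Background mentions bleeding and muscle damage as drawbacks of conventional surgery, without predicting a difference in drainage or creatine kinase.
- **That scar scores or the ODI analysis are affected in the same way.** Nothing in the text ties either to number of levels.

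What the replies do not remove is that the article commits to a method that cannot use a prognostic split created by its own eligibility rule.

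**Conclusion.** The point holds as a minor, inexpensive improvement to the analysis of four secondary outcomes. The unadjusted t-test is valid but may be inefficient. With a two-level share of 20% to 50% and a level difference of 0.5 to 2 within-level SDs, the variance factor is 1.04 to 2.0, and 80% power when adjusted becomes about 78% to 51%. Both ranges are assumptions, so the true loss could be negligible or large. The calculation also assumes the same level effect in both arms and the same spread within each level. A reader might infer that the comparisons are biased or the allocation faulty; neither follows. The sample size of 60 per group and the primary analysis are untouched.

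**What to change.** In the section on sample size and statistical analysis, replace Student's t-test for operation time, postoperative drainage, postoperative creatine kinase and admission duration with a prespecified linear model containing treatment group and planned number of levels (1 versus 2). Report the adjusted mean difference with its 95% confidence interval. Use the number of levels planned before randomisation, not the number finally operated on, so that the covariate cannot be influenced by the allocated technique. Fix this wording before the data are analysed by arm.

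The cost is one sentence and one degree of freedom (117 residual instead of 118 with all 120 patients). The planned number of levels should already be available from screening, and the named statistical package can fit the model. No extra patients, visits or procedures are needed. No change to the randomisation or to the ODI analysis is asked for.

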### Recruitment

Patients will be recruited if they are scheduled to undergo 1- or 2-level decompressive laminectomy for lumbar central canal stenosis in one of the six participating hospitals. Potential participants will be screened by a researcher to determine eligibility. A blinded assessor will conduct baseline assessments among the included patients. All participants will receive a baseline test and outcome assessment after giving written informed consent. No harm or adverse effects are anticipated, as outcome data will only be obtained using pre- and postoperative questionnaires and clinical and radiological assessments. Therefore, no incentives will be given to the study participants.

### Randomization

The included patients will be randomly assigned (permuted block method) in a 1:1 ratio to either the biportal endoscopic group (case group) or conventional group (control group), following a computer-generated randomization list (Fig. 1). The randomization lists will be incorporated into a web-based electronic case report form (eCRF) platform (iCReaT; internet-based clinical research and trial, icreat.nih.go.kr) accessible to authorized researchers. To minimize bias, randomization will be performed by the research coordinator who is not involved in the treatment of the patients. Sixteen surgeons from six institutions will be informed of each patient’s group allocation via the randomization code immediately before surgery. Patients will be aware of their group allocation because of the incision site after surgery. This RCT will be single-blind (assessor-blind).

**Fig. 1 Fig1:**
[figure not shown]
A diagram of patient flow in this study

### Operation technique

#### Case group: biportal endoscopy

The most critical aspect of the biportal endoscopic technique is that the procedure proceeds by securing a working space through two portals. Each portal is approximately 1 cm in size; one portal serves as the viewing portal, and the other serves as the working portal. The portals are positioned immediately lateral to the spinous process and separated by 1–1.5 cm. When operating on the patient’s left side, the viewing portal is positioned on the cranial side; the working portal is positioned on the caudal side and is within the interlaminar space. Using a Cobb elevator, the paraspinal muscle is detached from the spinous process and lamina to secure a working space. Subsequent laminectomy and flavectomy procedures are performed using the ULBD technique (Fig. 2) [5]. During the surgical procedure, continuous irrigation is performed through the viewing portal, with the pressure being adjusted to 30–40 mmHg.

**Fig. 2 Fig2:**
[figure not shown]
(**A**) A schematic diagram of biportal endoscopic surgery using a lumbar sawbone. (**B**) Preoperative magnetic resonance imaging. Red lines indicate the target cutting area for unilateral laminectomy bilateral decompression using the biportal endoscopic technique. (**C**) Postoperative well-decompressed state

#### Control group: conventional surgery

Decompressive laminectomy has a long track record of use for the treatment of lumbar central canal stenosis [13]. A midline incision of approximately 4 cm is made, and the paraspinal muscle is detached using the Cobb elevator. After securing the operation field using a Taylor retractor, the procedure is performed under a microscope. The bilateral decompressive laminectomy procedure is subsequently performed using a burr and Kerrison punches (Fig. 3). After removing the lamina and ligamentum flavum in the region with central canal stenosis, sufficient decompression of the dura and root is confirmed.

**Fig. 3 Fig3:**
[figure not shown]
(**A**) Preoperative magnetic resonance imaging. Red lines indicate the target cutting area for conventional bilateral decompressive laminectomy performed under a microscope. (**B**) Postoperative well-decompressed state

### Outcome measures

#### Primary outcome

The primary outcome will be the difference in Oswestry Disability Index (ODI) scores between baseline and at 1 year after surgery [14]. Among the wide range of patient-reported outcomes, the ODI is the most suitable for functional evaluation of the lumbar spine. Patients are instructed to provide an answer of 0–5 for each section in the ODI questionnaire, with a score of 5 representing the greatest disability. The total score is calculated as a percentage of the total maximum score (excluding questions with no responses). In cases where a patient provides two or more responses to a single question, the highest score will be counted.

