To date, most of the studies on the biportal endoscopic technique have utilized a retrospective study design and have only provided preliminary results. However, the results of two recent RCTs have been reported. Kang et al. found that the use of the biportal endoscopic technique in patients with LSS resulted in more favorable clinical outcomes, such as less postoperative pain and a shorter hospital stay, compared with the use of microscopic surgery [24]. In another RCT, Park et al. reported the non-inferiority of biportal endoscopic decompressive laminectomy to microscopic open surgery in patients with symptomatic LSS [18]; therefore, they suggested that the biportal endoscopic technique was a feasible option in this patient group.

Nevertheless, there are still some doubts regarding the efficacy of biportal endoscopic surgery in patients with LSS, as the majority of studies have been retrospective and utilized short-term follow-up assessments and small sample sizes at single centers. The results reported by the two aforementioned RCTs are insufficient to conclusively determine whether there are any differences in efficacy between biportal endoscopy and conventional microscopy.

To the best of our knowledge, this study will be the first multicenter, prospective RCT to compare the outcomes between biportal endoscopic and conventional microscopic decompressive laminectomy. However, this study protocol has some limitations. First, this is not a double-blind randomized controlled trial. As mentioned previously, the participant can learn the type of surgery performed based on the skin incision. Therefore, this study is a randomized, controlled, assessor-blind clinical trial. Second, the evaluation of pain control before and after surgery may be insufficient. Third, there is heterogeneity of treatments before surgery, and there will be differences between institutions and surgeons regarding pain control regimens chosen after surgery. This may cause inaccuracies in the evaluated clinical outcomes after surgery. Despite these limitations, the results of this trial will provide a high level of evidence for the efficacy and safety of the biportal endoscopic technique in patients with LSS and facilitate the development of clinical practice guidelines. Furthermore, the results of this study may indicate the feasibility of the biportal endoscopic technique for other types of spinal surgery.

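### The primary outcome is defined both as change in ODI and as 12-month ODI, and the SD behind the sample size fits the 12-month score, so planned power carries over to an unadjusted change score only if the baseline to 12-month correlation is about 0.5 or more

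*Protocol article*

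**What the plan says.** The Primary outcome section of the protocol article defines the endpoint as a change: "The primary outcome will be the difference in Oswestry Disability Index (ODI) scores between baseline and at 1 year after surgery". The Methods paragraph of the abstract defines it as a level at one time point: "The primary outcome (Oswestry Disability Index at 12 months after surgery) will be evaluated through a modified intention-to-treat method". Both are current text.

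The section on sample size and statistical analysis states that the aim is "to confirm the primary outcome equivalence between biportal endoscopic and conventional decompressive laminectomy". Its inputs are:

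- difference: "Previous studies have indicated a minimal clinically important ODI difference of 12.8"
- variability: "as well as a standard deviation of 18.8, at 1 year after endoscopic decompressive laminectomy"
- error rates and attrition: "alpha of .05, power of .90, two-sided confidence interval of 95%, and a 20% loss to follow-up"

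The result is 60 per group. No SD of change and no baseline to 1-year correlation is given. The methods named there are repeated measures ANOVA for secondary outcomes, and Student's t-test or chi-square for other outcomes and adverse events. No between-group test is tied explicitly to the primary outcome. Table 1 shows ODI collected at screening and at every follow-up visit.

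**The concern.** The 12-month score and the change from baseline are different analysis variables. Under randomisation their unadjusted comparisons target the same between-group difference. In any one sample, however, they give different estimates, confidence intervals and P values whenever the groups differ by chance at baseline. If both definitions stand, a reader of the results cannot tell which was pre-specified.

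They also differ in precision. An SD for the 1-year score says nothing about the SD of change unless the correlation with baseline is known. If the trial follows the definition in the Primary outcome section and compares raw changes, the power the article states may not apply.

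**Working it through.** **Inputs from the protocol article:** difference or margin 12.8; SD 18.8 at 1 year; two-sided alpha 0.05; power 0.90; 20% loss; 60 per group, so 60 × 0.8 = 48 evaluable per group.

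**Assumptions, not in the article:** the correlation r between baseline and 12-month ODI, taken over 0.3 to 0.7; and a baseline SD equal to the 12-month SD, relaxed at the end.

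**Step 1. Reproduce the stated number.** Two-sided comparison of means:

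n = 2 × [18.8 × (1.960 + 1.282) / 12.8]² = 45.3, so 46 per group; 46 / 0.8 = 57.5, so 58.

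The t-based version needs 47, and 47 / 0.8 = 58.75, so 59. Either is close to the stated 60. The number therefore reproduces when 18.8 is the SD of the variable analysed, as it is for an unadjusted comparison of 12-month scores.

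**Step 2. SD under each analysis.**

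- Unadjusted 12-month score: 18.8 at any r
- Unadjusted change: 18.8 × √(2(1 − r))
- ANCOVA on baseline: 18.8 × √(1 − r²)

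The change SD equals 18.8 exactly at r = 0.5. It is larger below that and smaller above.

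**Step 3. Power with 48 per group.** The two-sided column uses the t-test at 0.05 with a true difference of 12.8. The equivalence column requires the 95% CI to lie within ±12.8 when the true difference is 0 (two one-sided t-tests at 0.025).

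| r | SD, change | SD, ANCOVA | Two-sided: change v ANCOVA | Equivalence: change v ANCOVA |
|---|---|---|---|---|
| 0.3 | 22.2 | 17.9 | 80% v 93% | 59% v 87% |
| 0.4 | 20.6 | 17.2 | 85% v 95% | 71% v 90% |
| 0.5 | 18.8 | 16.3 | 91% v 97% | 82% v 94% |
| 0.6 | 16.8 | 15.0 | 96% v 98% | 92% v 97% |
| 0.7 | 14.6 | 13.4 | 99% v 99.6% | 98% v 99% |

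The reference at every r is the unadjusted 12-month score: 91% two-sided, 82% equivalence.

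**Step 4. Read against the reference.** At r = 0.5 the change score has the same power as the 12-month score on both bases, so the 82% there is not a change-score penalty. The distance from 90% to 82% comes from judging equivalence with a 95% CI, whichever endpoint is used. The loss due to the change score is the gap below 91% or 82%, and it exists only for r below 0.5. At r = 0.3 it is 11 points (two-sided) or 23 points (equivalence).

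**Step 5. Unequal SDs.** If the baseline SD is k times the 12-month SD, the change SD is 18.8 × √(1 + k² − 2rk), which is at most 18.8 when r ≥ k/2. At r = 0.3:

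- k = 0.75: SD 19.8, power 88% two-sided and 76% equivalence
- k = 1.25: SD 25.3, power 69% two-sided and 38% equivalence

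**Step 6. Why ANCOVA removes the ambiguity.** With treatment T, baseline Y₀ and 12-month score Y₁, the model Y₁ = a + bT + cY₀ can be rewritten as Y₁ − Y₀ = a + bT + (c − 1)Y₀. The treatment coefficient b and its standard error are the same whichever response is used.

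**The case against.** The strongest reply is that this is a mismatch between abstract and body, that the body's definition is explicit, and that both versions estimate the same treatment effect. That is fair as a limit on the consequences. It does not remove the contradiction, because the SD used for sizing fits the abstract's version and not the body's.

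Several stronger readings are tempting and are not supported:

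- **The trial is underpowered.** This depends on r and the baseline SD, neither of which is in the article. From r = 0.6 up, with equal SDs, the change score beats the unadjusted 12-month score and comes within about 5 points of ANCOVA.
- **The sample size is a miscalculation.** The 60 per group reproduces to within one or two patients on a two-sided test.
- **The trial is committed to an unadjusted change score.** No between-group test is tied to the primary outcome, and a change endpoint can itself be analysed by ANCOVA. The unadjusted analysis is an inference from the endpoint wording.
- **Leaving out hospital and number of levels as covariates is an error.** A condensed article commonly leaves covariates to the analysis plan. The remark in the Discussion that "there will be differences between institutions and surgeons regarding pain control regimens chosen after surgery" discloses a limitation about pain control and says nothing about modelling.

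**Conclusion.** The point holds in a limited form. The primary endpoint is defined in two ways, and the SD of 18.8, on its natural reading, belongs to the 12-month version. That needs no outside assumption beyond the reading of the SD.

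The effect on power is conditional. With equal SDs, the planned power carries over to an unadjusted change score only for r of about 0.5 or more. At r = 0.3 it falls to 80% against 91% for the 12-month score on the two-sided test, and to 59% against 82% for equivalence. At r = 0.7 it is higher than the 12-month score on both bases. Baseline-adjusted ANCOVA is at least as powerful as either unadjusted analysis across the range shown. That advantage is a large-sample property, and with 96 evaluable patients the cost of estimating one slope is negligible.

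The inconsistency should be corrected. It does not show that the trial is too small.

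**What to change.** State one primary endpoint: the between-group difference in ODI at 12 months, estimated by ANCOVA adjusted for baseline ODI, with its 95% CI. Use that definition in the abstract, the Primary outcome section and the sample size section, and say in the last that 18.8 is the SD of the 1-year score, if that is what the cited source reports. Change from baseline can still be described within each group, without a separate primary test.

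The cost is wording only. Baseline ODI is already scheduled at screening in Table 1, and this point calls for no extra patients or visits. Adjustment for hospital or number of levels is an optional choice for the analysis plan. Table 1 does not list number of levels as a recorded item, so its availability would need confirming first.
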